### Study Objectives

Consistent with the promising role of technology-based psychological interventions in addressing CUD in individuals with psychosis, we developed a psychological mobile app–based intervention (iCanChange [iCC]) and a pilot randomized controlled trial (RCT) to compare iCC with EIS in participants with FEP. The primary objectives are to assess intervention completion and trial retention rates. The secondary objectives are to conduct a preliminary assessment of the effect of iCC on the quantity of cannabis used, participant satisfaction, and app use and to evaluate trial recruiting parameters. We include exploratory outcomes (eg, psychotic symptoms, motivation to change cannabis consumption, and cannabis use protective behaviors) to strengthen our understanding of the benefits of using iCC in clinical settings.

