## Methods

### Study Design

This study is a two-arm, parallel group (1:1 ratio) pilot RCT of iCC for decreasing cannabis use and modified Early Intervention Services for psychosis (mEIS) compared with EIS for young adults with FEP. Study participation may last up to 28 weeks and include a 14-day screening period (with an additional 14-day window to complete the baseline assessments), a 12-week intervention period, and a 12-week booster session and follow-up period (Figure 1). The CONSORT-EHEALTH (Consolidated Standards of Reporting Trials of Electronic and Mobile Health Applications and Online Telehealth) [43] guidelines were used to describe the protocol.

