
### Sample Size

Sample size calculations were guided by the results of studies that used psychological app-based interventions targeting cannabis use in individuals without psychosis [68] or with subthreshold psychosis [38], in which attrition was lower than 33% and the intervention completion rate was approximately 50%. We will use a CI approach with binomial SEs and normal approximation [69] to calculate the number of participants needed to reject the null hypothesis that at 12 weeks, the attrition will be ≥50% (expected maximum attrition of 30%) and intervention completion will be ≤50% (the minimum expected proportion of participants who download the app and complete at least 11 out of 21 intervention modules—excluding the 3 boosters—is 70%). We calculated that at least 33 participants must be randomized per study arm to maintain 80% power to detect hypothesized effects with a 1-sided significance level of 5%. For the intervention completion outcome, we adjusted the sample size for an estimated 30% attrition and calculated that a total of approximately 100 participants will be needed for this study (2 × 33 / 0.7 = 94).

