### Randomization and Blinding

Once baseline assessments are completed, participants will be randomized to either (1) iCC+mEIS or (2) EIS. Within each stratum, based on biological sex, a random 1:1 group allocation sequence is generated using a permuted block design with blocks of varying sizes to decrease the likelihood of predictability of group assignment. The group allocation will not be masked, and the baseline visit concludes with participants logging into iCC and completing the introductory module. If a participant drops out of the study at any point following randomization, the randomization slot will not be reallocated to a new participant. The randomization schedule is concealed within the secure REDCap system and was created by the CHUM Center for the Integration and Analysis of Medical Data (CITADEL). The study participants, clinicians, and research staff conducting assessments will not be blinded to the group assignment, while individuals performing analyses will be blinded.

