### Statistical Analyses

The 1-sided chi-square 95% CI will be calculated to estimate the lower bound of iCC completion and trial retention rates. We will consider participation in iCC acceptable if more than 50% of the participants completed at least 11 out of 21 intervention modules at week 12. The trial will be considered feasible if the attrition at week 12 does not reach 50%. An analysis of covariance model will be used to provide a preliminary assessment of the effect of treatment on the quantity of cannabis use (dependent variable) at 12 weeks (end of intervention). The independent variables will be the quantity of cannabis use at baseline and a dichotomous variable reflecting arm allocation. The second model will include covariates that were found to be different between the groups at baseline. For participants’ satisfaction with the intervention, we will calculate the CSQ total scores as well as the mean and SD. The groups will be compared using a mixed-effects model with random intercepts for each site. For app use and trial parameters, we will use univariate analyses and report the distribution (frequency tables), central tendency (mean, median, and mode), and dispersion (range and SD).

For exploratory outcomes, we will compute descriptive statistics and bivariate and multivariable analyses using generalized estimating equation (GEE) models. The generalized estimating equation is a repeated-measures regression model that accounts for the correlations between repeated measures for each person [70]. We will use different types of GEE modeling depending on the distribution of the outcome. For cannabis frequency (count data), we will use Poisson; for the abstinence (binary), we will use binomial; and for continuous variables (ie, scores calculated for MPS, SDS, DTCQ, PANSS, PBSM, SWL, and SPS), we will use linear GEE modeling. Using this analytic approach, we will estimate the multivariable associations between the outcomes and study visits (ie, baseline and end of intervention), study condition (the reference group will be the control arm), and their interaction, as well as other predictors and covariates, such as sociodemographics, social support, CUD severity, behavioral stage of change, medication status, and other substance use. We will use the chi-square test of proportions to compare behavioral stages at different time points and between the 2 study arms.

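### The week-12 cannabis-quantity ANCOVA omits sex, the randomisation stratum, and its second model adjusts for chance baseline differences; the cost is a modest, conservative loss of precision

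*Protocol article*

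**What the plan says.** **Randomisation** (Protocol article, Randomization and Blinding). "Within each stratum, based on biological sex, a random 1:1 group allocation sequence is generated using a permuted block design", with blocks of varying size. Sex is the only stratum named.

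**First efficacy model** (Statistical Analyses). "An analysis of covariance model will be used to provide a preliminary assessment of the effect of treatment on the quantity of cannabis use" at 12 weeks. Its terms are then listed: "The independent variables will be the quantity of cannabis use at baseline and a dichotomous variable reflecting arm allocation". Sex is not among them.

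**Second efficacy model** (same section). "The second model will include covariates that were found to be different between the groups at baseline".

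**Satisfaction** (same section). The arms are compared with a mixed-effects model that has a random intercept for site. Sex is not mentioned.

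**Exploratory outcomes** (same section). The generalized estimating equation (GEE) models may use predictors "such as sociodemographics, social support, CUD severity, behavioral stage of change, medication status, and other substance use". The Measurements section lists biological sex among the sociodemographic data, so these models already make room for it.

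**Status of the outcome** (Study Objectives). "The secondary objectives are to conduct a preliminary assessment of the effect of iCC on the quantity of cannabis used". The primary outcomes are intervention completion and trial retention.

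**The concern.** There are two faults, and the first makes the second worse.

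1. Stratified blocks make the arms more alike on sex than simple randomisation would. If sex predicts the outcome, the true variability of the arm difference falls. A model without sex leaves that variation in its residual and reports a standard error that is too large.

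2. Choosing covariates by observed imbalance uses the wrong criterion. In a randomised trial a baseline difference is due to chance and says nothing about whether the variable predicts week-12 use. The rule can admit irrelevant variables and pass over strong predictors that happen to be balanced. The content of the adjusted model is also unknown until the baseline table has been seen.

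Because the blocks balance sex, an imbalance rule will rarely select it. The stratification factor is therefore likely to be absent from both models.

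The Conclusions present the pilot as a source of data for designing a larger efficacy trial. The quantity estimate and its standard error are therefore worth getting right, even though no pilot decision depends on them.

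**Working it through.** **The plan's own figure.** No size or power is stated for the ANCOVA. The only calculation (Sample Size) is for feasibility: "at least 33 participants must be randomized per study arm". With 70% expected against 50% null, one-sided 5% and 80% power:

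n = (1.645 + 0.842)² × 0.7 × 0.3 / 0.2² = 32.46, so 33.

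Then 2 × 33 / 0.7 = 94.3, stated as 94 and taken as about 100. The figure reproduces, and nothing below changes it.

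**Step 1: standard error when a balanced stratum is omitted.** Let p be the male share and b the sex difference in residual SDs. In large samples

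reported SE / correct SE = √(1 + p(1 − p)b²).

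The value of p comes from the Introduction: 78%-86% male among people with first-episode psychosis and a comorbid substance use disorder. The value of b is assumed, because the documents give none. The true two-sided type I error is 2 × [1 − Φ(1.96 × ratio)].

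| b | p = 0.78, p(1 − p) = 0.1716 | p = 0.86, p(1 − p) = 0.1204 | True type I error at nominal 5% |
|---|---|---|---|
| 0.3 | 1.0077 | 1.0054 | 4.8%-4.9% |
| 0.5 | 1.0212 | 1.0149 | 4.5%-4.7% |
| 0.8 | 1.0535 | 1.0378 | 3.9%-4.2% |
| 1.0 | 1.0824 | 1.0585 | 3.4%-3.8% |

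For example, at b = 0.8 and p = 0.78: √(1 + 0.1716 × 0.64) = √1.1098 = 1.0535.

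**Step 2: simulation under no treatment effect.** The inputs from the protocol are 100 participants, 1:1 allocation in blocks within sex, and 30% dropout. The assumptions are block sizes 2, 4 and 6, random dropout, baseline correlation 0.5, ten candidate covariates each with coefficient 0.15, and selection at p < 0.05. There were 4,000 runs per scenario, so the Monte Carlo error of a 5% rate is √(0.05 × 0.95 / 4000) = 0.34 percentage points. Sex effects are on the outcome scale. The residual SD after baseline adjustment is √(1 − 0.5²) = 0.866, so 0.5 and 0.8 correspond to 0.58 and 0.92 residual SDs.

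Each cell gives true SD of the estimate / mean model SE / type I error.

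| Sex effect, male share | Model 1 as planned | Model 1 plus sex | Model 2 as planned |
|---|---|---|---|
| 0, 78% | 0.2062 / 0.2083 / 4.68% | 0.2067 / 0.2089 / 4.58% | 0.2041 / 0.2100 / 4.50% |
| 0, 86% | 0.2082 / 0.2082 / 5.10% | 0.2087 / 0.2088 / 5.12% | 0.2058 / 0.2099 / 4.70% |
| 0.5, 78% | 0.2104 / 0.2142 / 4.62% | 0.2087 / 0.2089 / 5.08% | 0.2074 / 0.2162 / 4.10% |
| 0.5, 86% | 0.2135 / 0.2131 / 5.10% | 0.2127 / 0.2095 / 5.45% | 0.2099 / 0.2149 / 4.32% |
| 0.8, 78% | 0.2146 / 0.2231 / 4.40% | 0.2093 / 0.2089 / 5.10% | 0.2127 / 0.2251 / 3.75% |
| 0.8, 86% | 0.2150 / 0.2191 / 4.35% | 0.2117 / 0.2091 / 5.00% | 0.2115 / 0.2210 / 3.88% |

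- At 0.8 and 78% male, model 1's SE is too wide by 0.2231 / 0.2146 = 1.040, or 4%. At 86% male it is 0.2191 / 0.2150 = 1.019, or 2%. Dropout partly undoes the balance on sex, so the excess is smaller than Step 1 suggests.
- Over all scenarios, including a sex effect of 1.2, model 2's type I error is 3.1%-4.7%.
- If significance in either model counts as success, the rate is at most 5.8%.

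**Step 3: what a fixed list gains.** With sex and all ten covariates fixed in advance, the spread of the estimate falls from about 0.21 to about 0.19, with type I error 4.7%-5.6%. The size of this gain depends on the assumed covariate strengths and on using all ten. A shorter list would gain according to how prognostic its members are.

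**Step 4: how often the rule adds something.** If differences were judged at p < 0.05 among k independent covariates, at least one would enter with probability 1 − 0.95^k: 23% for k = 5, 40% for k = 10 and 54% for k = 15. The protocol states neither k nor a threshold.

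**The case against.** The case for leaving the plan alone is a serious one.

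- **The harm is small, in the safe direction and conditional.** It needs a sex effect on quantity that the documents do not report. If sex is not prognostic, omitting it costs nothing. This stands, and it sets the size of the point.
- **Little depends on it.** Quantity is a secondary outcome and the analysis is called preliminary. The first model is not data-selected. The limitations paragraph acknowledges the weakness of pilot efficacy estimates. Acceptability and feasibility rest on completion and attrition. This also stands.
- **A statistical analysis plan may exist.** A candidate list or a threshold for calling groups different could sit there, so their absence here is not criticised. The list of model 1 terms and the imbalance rule, however, are stated in the article and can be judged as stated.
- **Analysts are blinded.** Neutral group labels limit deliberate steering, but an imbalance is just as visible between two unnamed groups, so the rule works the same way.

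Three stronger readings are tempting, and the documents do not support them.

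- A reader might infer that confidence intervals from the second model are invalid or that false positives are inflated. Selection uses baseline data only, not week-12 outcomes, and the simulated errors are conservative.
- A reader might take the 40% or 54% in Step 4 as an error rate. It is only the chance that some covariate enters the second model, and adjusting for a chance-imbalanced baseline variable does not by itself bias a randomised comparison. It also presumes a 5% test and independent covariates, and several of the collected measures are related.
- A reader might extend the omission of sex to the exploratory models. Their covariates already include sociodemographics, and biological sex is collected as one of them.

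**Conclusion.** The point holds as one about specification and precision. The protocol stratifies on sex, then lists an ANCOVA without it and fills the second model by a criterion unrelated to prognosis that will seldom bring sex in. The satisfaction model does not name sex either.

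The large-sample excess in the standard error is about 1.5-2% for a sex difference of 0.5 residual SD and about 4-5% for 0.8. It is close to zero if sex does not predict quantity. The error makes intervals slightly too wide and does not materially raise the false-positive rate. The imbalance rule also forgoes whatever precision would come from prognostic covariates that happen to be balanced.

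These sizes rest on the assumed sex effect and on a male share of 78%-86% carried over from the Introduction. The simulated figures also depend on the assumed baseline correlation, covariate strengths, selection threshold, block sizes and random dropout. The primary outcomes, the feasibility decisions and the sample size are untouched. The change is worth making because it is nearly free, not because the present plan would mislead.

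**What to change.** 1. Add biological sex to both ANCOVA models for week-12 quantity and to the satisfaction model, keeping the random site intercepts in the latter.
2. Replace the imbalance rule for the second model with a short list of covariates chosen on prognostic grounds, for example baseline quantity, sex and baseline Severity of Dependence Scale score. Fix the list before unblinding, and preferably before any baseline table by arm is produced, even one with masked labels.
3. Report baseline characteristics by arm descriptively, without significance tests, and do not use them to choose covariates.

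The exploratory GEE models need no change on this point. The cost is a sentence or two in the analysis section and a few degrees of freedom, with about 70 of 100 participants expected at week 12 (100 × 0.7). Recruitment, conduct and sample size do not change.

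### The linear GEE models for the exploratory scale scores compare arms by difference in change with a free baseline arm effect; the contrast is unbiased but less precise than one that uses the baseline score

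*Protocol article*

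**What the plan says.** In the protocol article, Statistical Analyses, the exploratory outcomes are handled as follows: "we will compute descriptive statistics and bivariate and multivariable analyses using generalized estimating equation (GEE) models". The terms are "study visits (ie, baseline and end of intervention"), then "study condition (the reference group will be the control arm), and their interaction, as well as other predictors and covariates". The covariates are given by example: "such as sociodemographics, social support, CUD severity, behavioral stage of change, medication status, and other substance use". An outcome's own baseline score is not listed as a general covariate.

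The model type depends on the outcome. For the continuous measures the text reads "scores calculated for MPS, SDS, DTCQ, PANSS, PBSM, SWL, and SPS), we will use linear GEE modeling". For the other two it reads "For cannabis frequency (count data), we will use Poisson; for the abstinence (binary), we will use binomial".

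The same section treats cannabis quantity at 12 weeks differently, by analysis of covariance: "The independent variables will be the quantity of cannabis use at baseline and a dichotomous variable reflecting arm allocation". Its missing-data paragraph keeps in the GEE models anyone with at least one observed visit. Randomization and Blinding fixes the order of events: "Once baseline assessments are completed, participants will be randomized".

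**The concern.** With visit, arm and arm-by-visit in the model and baseline as one of the two visits, the arm main effect is the baseline difference between arms, estimated freely. The interaction is then the difference between arms in change from baseline, and it is the only term that compares the arms over time.

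In a randomised trial whose baseline is taken before allocation, the true baseline difference is zero. Estimating it adds variance and gains nothing. It also lets a chance imbalance at baseline pass into the effect estimate. For cannabis quantity the plan already uses the baseline value as a covariate, and the article gives no reason for treating the scale scores otherwise. At stake are the width of the intervals for seven scale scores and the steadiness of estimates that the authors want to carry into the design of a larger trial.

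**Working it through.** **Inputs from the protocol.** About 100 participants allocated 1:1, so 50 per arm; expected maximum attrition of 30% at week 12 (Sample Size), so 35 per arm with a week 12 score; two visits, baseline and end of intervention (Statistical Analyses).

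**The plan's own figure.** The stated sample size reproduces: (1.645 + 0.842)² × 0.7 × 0.3 / 0.2² = 32.5, so 33 per arm, and 2 × 33 / 0.7 = 94, rounded to about 100. It concerns completion and attrition only. The protocol gives no SD, correlation or power for the exploratory scores.

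**Assumptions.** Unit variance at both visits, and a baseline-to-week-12 correlation r of 0.3, 0.5 or 0.7.

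**Formulas.** Let X be the baseline score and Y the week 12 score. Y − rX is uncorrelated with X. With everyone's baseline in the model and the correlation used:

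- Free baseline arm effect (as planned): each arm contributes the mean of Y − rX over 35 people minus (1 − r) times the mean of X over 50. Per-arm variance = (1 − r²)/35 + (1 − r)²/50.
- Common baseline mean: the second part is the same in both arms and cancels. Per-arm variance = (1 − r²)/35.

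| r | Free baseline | Common baseline | Ratio | Variance cut |
|---|---|---|---|---|
| 0.3 | 0.0260 + 0.0098 = 0.0358 | 0.0260 | 0.73 | 27% |
| 0.5 | 0.0214 + 0.0050 = 0.0264 | 0.0214 | 0.81 | 19% |
| 0.7 | 0.0146 + 0.0018 = 0.0164 | 0.0146 | 0.89 | 11% |

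**Simulation check.** Exchangeable GEE, 50 per arm, 30% dropout at week 12, a true effect of −0.40 SD, a baseline covariate entered as a main effect, 400 runs per setting. Mean standard errors, planned against common baseline, were 0.266 and 0.229 (r = 0.3), 0.226 and 0.205 (0.5), and 0.180 and 0.170 (0.7). All models were unbiased, and the covariate did not recover the loss. Week 12 regression on arm and baseline score gave 0.230, 0.207 and 0.172.

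**Complete data.** With no dropout the comparison is 2(1 − r) against 1 − r², a ratio of (1 + r)/2: 0.65, 0.75 and 0.85.

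**Chance imbalance.** A baseline difference δ between arms moves the planned estimate by −(1 − r)δ relative to the adjusted one. With 50 per arm the standard error of δ is √(2/50) = 0.20 SD. At r = 0.5 a one-standard-error imbalance therefore moves the estimate by 0.10 SD. The only effect size the protocol cites is 0.19, for quantity of cannabis (Study Strengths and Challenges).

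**Working correlation.** Under working independence, dropping the arm effect leaves the raw week 12 difference, with per-arm variance 1/35 = 0.0286. The planned model under independence has 1/35 + 1/50 − 2r/50. At r = 0.7 this is 0.0206, so the change would make matters worse. At r = 0.5 it is 0.0286, so nothing is gained.

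**The case against.** An arm-by-visit GEE is a standard, valid model, and randomisation makes its interaction unbiased. The outcomes are exploratory in a pilot whose primary outcomes are completion and retention. The one cannabis measure singled out for a preliminary effect estimate is already adjusted for baseline. The authors acknowledge the limits of efficacy estimates from a pilot and promise to interpret them with care. The article speaks of multivariable associations, leaves the covariate list open, and does not name the interaction as the treatment effect. The correlations used here are assumed.

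Much of this stands, and it limits the weight of the point to minor. It does not remove the loss. The terms are stated, and with them no other contrast compares the arms over time. The open covariate list does not help: a time-constant covariate entered as a main effect does not sharpen the interaction, and this holds even for an outcome's own baseline score while baseline remains a response row.

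Some stronger readings are tempting but not supported:

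- A reader might infer that at a correlation of 0.5 the planned contrast is no better than ignoring baseline. That is exact only with complete data (2 × 0.5 = 1). With 50 baselines and 35 week 12 scores, the planned variance is 0.0264 against 0.0286 when baseline is ignored, so keeping everyone with at least one visit already recovers part of the loss.
- A reader might infer that the plan contradicts itself by using covariance analysis for quantity and GEE for the scales. Both are valid, and using different models for different outcomes is not a contradiction.
- A reader might extend the argument to cannabis use frequency and abstinence. There the interaction is a ratio of rate ratios or of odds ratios, and the variance formulas above do not apply.

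**Conclusion.** The point holds as a minor matter of precision in the linear GEE models. The planned contrast is unbiased but needlessly wide. With 50 per arm at baseline and 35 at week 12, a common baseline mean lowers the variance by about 27%, 19% and 11% at correlations of 0.3, 0.5 and 0.7, which makes the intervals about 15%, 10% and 6% narrower. The figures rest on the assumed correlations, equal variances at the two visits, and a working correlation other than independence.

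It would be wrong to conclude that the trial's main results are at risk: no primary conclusion, sample size or feasibility rule depends on these scores. Nor does the gain rescue power for small effects. At the cited effect of 0.19 and r = 0.5, normal-approximation power at a two-sided 5% level rises only from about 13% to 15%. The benefit is narrower intervals and less influence of chance imbalance.

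**What to change.** In the linear GEE models for MPS, SDS, DTCQ, PANSS-6, PBSM, SWL and SPS:

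- Keep visit and arm-by-end-of-intervention, and drop the arm main effect at baseline, so that both arms share one baseline mean.
- State an exchangeable or unstructured working correlation with robust standard errors, and rule out independence.
- Report the baseline-adjusted arm difference at end of intervention as the treatment effect.

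This still includes everyone with at least one visit, as the missing-data paragraph requires. The alternative is to regress the week 12 score on arm and the participant's baseline score, as the plan already does for cannabis quantity. Precision is nearly the same, but participants without a week 12 visit are left out, so the common-baseline model fits the plan better.

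The cost is a sentence or two of model wording, with no new data, participants or assessments.
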